### Statistical analysis

#### Primary analyses

The following hypothesis will be tested: H0: μ manualized ≤ μ standard *vs.* H1: μ manualized > μ standardwhere μ manualized and μ standard are the true remission probabilities in the manualized treatment group and the standard routine care group after the treatment period, respectively.

Remission rates will be compared between specifically trained and standard CBT group via logistic regression using covariates for treatment, sex of the therapist, and experience of the practitioner (as in
[37]). For repeated measures, as suggested by 
Wood *et al.*[46], random effects models will be fitted of outcomes taking into account potential drop-outs (for further reference, see
[42] and
[47]). Hypothesis 1 of this trial will be tested by the group*time interaction (with dummy variables coding the time effects at time points T4 to T7 as compared to baseline measurement).

Further analyses will include: comparison of remission rates across treatment groups at time points T4 to T7 using the chi-squared test of independence; cross-sectional analyses at T4 to T7 comparing both patients and therapists in the three study centers; analyses of covariance of outcomes at T4 to T7 considering patient variables, taking into account potential differences between patients recruited by trained *vs.* those recruited by non-trained therapists; and multiple regression analyses to test whether diverse covariates including process variables predict different treatment outcomes. Regression analysis will be applied to each treatment group separately. Should the results be similar, the sample will be pooled.

A descriptive analysis will be made on drop-outs and their covariates. Imputation methods will be considered if necessary following an assessment of the missing value structure
[46].

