**Methods/design:**

Thirty-six private practitioners will be included in three treatment centers and randomly designated to either training in manualized CBT or no specific training. The treatment effects of the therapies conducted by both groups of therapists will be compared. A total of 162 patients (*n* = 116 completers; *n* = 58 per condition) will be enrolled. Liebowitz Social Anxiety Scale (LSAS) will serve as primary outcome measure. Remission from social phobia is defined as LSAS total ≤30 points. Data will be collected at treatment begin, after 8, 15, and 25 sessions (50 min each), at treatment completion, as well at 6 and 12 months post-treatment.

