### Sample size calculation

The only study directly comparing performance of therapy delivered under RCT conditions and routine care refers to group CBT for social phobia
[18] and showed a small but significant advantage for the RCT therapies. The difference between the Clark trials
[17,18] and other controlled trials suggests a much higher difference in the to-be expected between-group effect sizes of our study but only under the improbable assumption that trained private practitioners will be comparably successful as the specialized therapists in the Clark trials. Sholomskas *et al.*[39], in a study directly testing the effects of additional training, but not in the field of SP, reported an average between group effect size of d = 0.69 when comparing therapists who were trained in a seminar plus supervision and therapists who used a manual without further training with regard to their performance in standardized role plays. However, this estimation does not directly refer to the expected effect sizes for the therapeutic benefit, which is the main outcome criterion of this trial. Given this inconsistent information, we choose to expect a more conservative effect size of d = 0.50 between Group 1 (trained therapists) and Group 2 (treatment-as-usual), for pragmatic reasons. We aimed at estimating the sample size needed for a dichotomous approach (remission rates according to the above defined criterion, LSAS <30). In order to assure comparability with the parallel trial for psychodynamic therapy
[37] we introduced the same conservative assumptions: (1) the ICC was set to 15% which is high compared to similar studies
[40]; and (2) for the primary analysis (ITT) drop-outs will be analyzed as patients with no remission. When assuming <50% remitters and an equal drop-out rate in both conditions, the absolute difference between remission rates will remain unchanged, but the relative difference will be much greater and will substantially enlarge the difference between treatments.

In contrast to Wiltink *et al.*’s study protocol
[37], the average number of patients in a cluster was assumed to be five, as we choose to collaborate more continuously with the included therapists. Please note that this is the only assumption differing from those made in
[37] resulting in a higher *a priori* sample size than in
[37].

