In order to detect a difference between Groups 1 and 2 at α = 0.05 (one-tailed; see Discussion) with a power of 0.80, *n* = 58 patients per group are required according to the formula of Campbell *et al.*[40,41] for cluster-randomization, given that five patients per therapist will be treated (for a more comprehensive account, see
[42]):

$$N=2*{\left[\frac{\sigma (z_{\alpha }+z_{\beta })}{E}\right]}^{2}*\left[1+(m-1)\rho \right]=2*{\left[\frac{\left(z_{\alpha }+z_{\beta }\right)}{ES}\right]}^{2}*\left[1+(m-1)\rho \right]$$

(z_α_, z-value for probability of error type I alpha; z_β_, z-value for probability of error type II beta; σ, standard deviation of outcome; E, expected ES of outcome; m, mean observations for each cluster; ρ, Intracluster correlation coefficient (ICC); ES = E/σ, standardized effect size)

Given a conservative drop-out rate estimate of 25% (taking into account slightly elevated drop-outs in a practice study), a total of *n* = 162 patients are required to be allocated to the trial. Thus, *n* = 54 patients will have to be included in each center. According to data of the [name] *et al.*[43] study on social phobia, in which patients were recruited in a comparable setting of German psychotherapeutic care, 61% of 250 patients meeting the inclusion criteria can expected to be finally included. We estimate that not more than about 250 patients will have to be assessed for eligibility.

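### The primary remission model states no term for the therapist as a cluster, so under the protocol's own ICC of 0.15 the nominal one-sided 5% test runs at about 9–10%

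*Protocol article*

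**What the plan says.** The Randomization section allocates therapists, not patients, to training or routine care; patients then choose a therapist freely. The abstract gives the number of clusters: "Thirty-six private practitioners will be included in three treatment centers".

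The Sample size calculation section treats patients of one therapist as correlated. It states that "the ICC was set to 15% which is high compared to similar studies" and that "the average number of patients in a cluster was assumed to be five", and the printed formula carries the factor [1+(m−1)ρ].

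The Primary analyses section states a one-sided null hypothesis on remission probabilities and compares remission rates "via logistic regression using covariates for treatment, sex of the therapist, and experience of the practitioner", with a reference to the companion psychodynamic trial. The next sentence opens with repeated measures and says that "random effects models will be fitted of outcomes taking into account potential drop-outs"; no level is given for the random effect. Hypothesis 1 is then assigned to the group-by-time interaction. Further analyses include "comparison of remission rates across treatment groups at time points T4 to T7 using the chi-squared test of independence".

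**The concern.** The sample size section and the analysis section rest on different assumptions. The first says that outcomes of patients who share a therapist are correlated, and by how much. The second describes a logistic regression on patients in which no term represents the therapist as a cluster. Sex and experience are fixed covariates at therapist level. They leave in the error whatever therapist variation they do not explain, and nothing in the article suggests that they explain an ICC of 0.15.

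When treatment is assigned by therapist and this variation is ignored, the standard error of the treatment effect is too small. The error has one direction: it favours a finding that training works. The test is already one-sided at 0.05, and the Abstract presents the results as relevant to healthcare policy, so control of that error rate matters.

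**Working it through.** **Inputs.** From the Sample size calculation section: "at α = 0.05 (one-tailed; see Discussion) with a power of 0.80"; "we choose to expect a more conservative effect size of d = 0.50"; ICC ρ = 0.15; m = 5; 58 per group required; 162 enrolled; drop-outs counted as non-remitters in the primary intention-to-treat analysis. From the abstract: 36 therapists. Because drop-outs stay in the analysis, the average cluster is 162/36 = 4.5. Assumptions: 18 therapists per arm (the ratio is not stated) and, for simulation, remission of 25% to 35% (the article says only below 50%).

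**The plan's own figure.** The printed formula is N = 2[(z_α+z_β)/ES]² × [1+(m−1)ρ].

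- Without clustering: 2 × [(1.645+0.842)/0.5]² = 49.5.
- Design effect: 1 + 4 × 0.15 = 1.6.
- Product: 49.5 × 1.6 = 79.1, so 80 per group.

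The stated 58 is not reproduced. Under this formula it would need an ICC of about 0.043 at m = 5, or about 2.2 patients per therapist at ICC 0.15. This is a separate defect. The size calculation below does not depend on it, but the cost of the fix does.

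**Size of a test that ignores the cluster.** With design effect DE, the true one-sided size is 1 − Φ(1.645/√DE).

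| ICC | m | DE | True one-sided size |
|---|---|---|---|
| 0.15 | 5 | 1.600 | 9.7% |
| 0.15 | 4.5 | 1.525 | 9.1% |
| 0.15 | 3.2 (116 completers / 36) | 1.333 | 7.7% |
| 0.10 | 4.5 | 1.350 | 7.8% |
| 0.05 | 5 | 1.200 | 6.7% |
| 0.05 | 4.5 | 1.175 | 6.5% |

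At ICC 0.15, standard errors are too small by a factor of √1.525 = 1.23 to √1.6 = 1.26. A nominal two-sided 5% chi-squared test would run at 11.2% to 12.1%.

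**Simulation check.** Remission was generated as beta-binomial with ICC 0.15 and no treatment effect. It was analysed by ordinary logistic regression on treatment, therapist sex and experience, with sex and experience unrelated to outcome (8,000 trials per setting, one-sided Wald test).

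- 36 therapists, 4.5 patients each: 8.9% (remission 25%) and 9.6% (remission 35%).
- 36 therapists, five patients each: 9.8%.
- Unequal cluster sizes, as free patient choice would produce: 10.7%.
- 116 completers only: 7.7%.
- ICC near zero (5,000 trials): 5.3%.
- A t test on therapist-level remission rates, in the settings with ICC 0.15: 4.5% to 5.0%.

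**Power once clustering is respected.** With 58 per group and DE 1.6, the effective number is 58/1.6 = 36.25 per group. Power is Φ(0.5 × √(36.25/2) − 1.645) = Φ(0.484) = 68.6%.

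**The case against.** **An unseen document may supply the therapist level.** The article is condensed. The logistic sentence points to the companion trial, and the random effects sentence cites a reference that the sample size section also cites for the cluster formula. An analysis plan may exist. It follows that a reader may not infer that the trial will certainly be analysed without clustering. The point still stands about the text: the article names the primary model and its covariates, and separately names a test that assumes independence. Both conflict with its own sample size assumptions.

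**The random effects models already cover it.** As described, they serve repeated measures and drop-out. A random effect for the patient does not represent correlation between patients of the same therapist.

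**Hypothesis 1 is assigned to the group-by-time test.** This is correct. A reader might take 9–10% as the error rate of every claim that training works. The figure belongs to the remission comparison only; no error rate was computed for the interaction test. The clustering gap applies there too, because no therapist level is stated.

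**The ICC is a cautious planning value.** The protocol calls it high, so an unconditional statement that false positives occur about twice as often as claimed is not supported. At ICC 0.05 the inflation is modest.

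**Randomisation is stratified by centre.** Any part of the ICC that lies between centres is balanced by design. A stratified simulation (36 therapists, 162 patients, remission 30%, ICC 0.15, unadjusted logit test) gave 8.9% with no centre share, 7.7% with an assumed 20% share and 7.1% with an assumed 40% share. Unequal cluster sizes push the other way.

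**The chi-squared tests are supporting analyses.** This is so. They repeat the fault but do not carry the point.

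**Conclusion.** The concern holds for the analysis as written. The stated remission comparison does not account for the therapist clustering that the sample size section assumes. Its nominal one-sided 5% test runs at about 9–10% if the ICC is 0.15 with 4.5 to five patients per therapist, and at about 6.5% if the ICC is 0.05. These figures assume that sex and experience explain little of the therapist variation, that cluster sizes are roughly equal and that little of the ICC lies between centres. In every setting with a non-zero ICC that was examined, the error was above 5%. Because it concerns a primary test, it should be corrected before analysis.

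**What to change.** - **Remission:** use a method that accounts for the therapist, for example logistic regression with a therapist random intercept, or GEE clustered on therapist with a small-sample correction for about 36 clusters. Other valid cluster methods would also do.
- **Group-by-time models for Hypothesis 1:** include therapist-level variation in change (therapist-by-time), with patients nested in therapists. A therapist intercept alone is not enough: it is common to baseline and later visits, so it drops out of the change that the interaction tests.
- **Chi-squared tests at T4 to T7:** replace them with the same cluster-adjusted comparison.

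No new data are needed, but the change is not free. Confidence intervals widen and power falls. The stated 58 per group does not meet the printed formula (80 per group) and gives about 69% power instead of 80%. The 162 enrolled are 81 per group, and with DE 1.6 that gives about 81% power, but only if d = 0.50 holds across all enrolled patients, including drop-outs counted as non-remitters. The sample size section should restate the power for the analysis actually used.

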### Participants

Patient inclusion and exclusion criteria are listed in Table
1. The sample fulfilling these criteria are considered representative for social phobia patients qualifying for treatment in an outpatient setting. Assuming a drop-out rate of 25% over a period of 2 years, a total of 162 patients are planned to be enrolled in the study (that is 54 patients in each center; see sample size calculation). Patients will only be able to enrol once in the present trial. Participants will be able to directly contact the trial centre in response to advertisements via the internet, flyers, or newspaper articles. Alternatively, they will be referred to by healthcare practitioners (that is, medical doctors or private practitioners in psychotherapy). Once the diagnostician confirms the patient’s eligibility for the study, the patient will select and contact a therapist from a list of candidates for treatment. Only private practitioners officially listed in the German chambers of psychotherapists will be recruited. Informed consent from both the therapist and the patient will be collected. All therapists will have to be certified in CBT. Inclusion criteria for therapists are broad (that is, any age and gender, living in the area of the trial center) as a function of the naturalistic aspects of the present trial. However, practitioners having recent training (within the last 5 years) in the Clark and Wells treatment of SP
[17] will be excluded from the study. Measures of allegiance to the treatment condition and professional experience will be collected via self-report of the therapists as well as via expert ratings of video-documented sessions.

**Table 1 T1:** Inclusion and exclusion criteria

**Inclusion criteria**	Diagnosis of SP (SCID-I)
	Liebowitz Social Anxiety Scale >30 (>60 for generalized subtype)
	Age 18 to 70 years
	SP must be primary diagnosis (most severe disorder according to ADIS-IV)
	SP patients with co-morbid disorders will be included, provided that SP is the primary diagnosis, thus ensuring a clinically representative sample as well as analyses of subgroups (for example, type of SP, patients with co-morbid depressive disorder)
**Exclusion criteria**	Psychotic disorder
	Prominent risk of self-harm
	Acute substance-related disorders
	Personality disorders except for avoidant
	Obsessive-compulsive or dependent personality disorder (SCID-II) organic mental disorder
	Severe medical conditions

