### Randomization

Therapists will be randomly assigned either to a training group (manualized CBT), in which they will undergo an intensive training of the treatment manual for social phobia, or to a control group (routine care), in which the non-manualized CBT standard treatment is applied. Private practitioners will be block randomized. Practitioner randomization will be stratified for each trial center using the nQuerie Advisor® 6.01 software program
[44]. As participants in a naturalistic study, patients are not randomized and have no knowledge on whether or not the therapist they have freely chosen has been trained in manualized CBT. Diagnostic procedures are performed by independent, blinded, and specially trained assessors for diagnosis and observer-rated outcome measures. All diagnosticians are trained by one of the co-authors (US), who was responsible for quality assurance of CBT in the SOPHO-NET study and has extensive experience in conducting RCT of SP
[43,45]. There will be multimethod assessment of specific and non-specific therapy outcome including both patient and assessor perspective; control for drop-outs, intent-to-treat analyses. Generalizability of results will be established by above defined inclusion and exclusion criteria (Table
1) and by the multicenter approach.

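### The logistic model for remission adjusts for therapist variables only, so any arm difference in patients' baseline severity or subtype stays unadjusted in that estimate

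*Protocol article*

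**What the plan says.** Under Randomization, the protocol article states that "Practitioner randomization will be stratified for each trial center" and that "patients are not randomized and have no knowledge on whether or not the therapist they have freely chosen has been trained" in the manualised treatment. Under Participants, a diagnostician first confirms eligibility, and the patient then picks a therapist from a list. Patients may also reach the trial by referral from practitioners, including private psychotherapists.

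Table 1 sets the entry threshold at "Liebowitz Social Anxiety Scale >30 (>60 for generalized subtype". Outcomes defines remission as an LSAS total of 30 or less.

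Primary analyses states the hypothesis in terms of quantities that "are the true remission probabilities in the manualized treatment group and the standard routine care group after the treatment period". Remission rates are compared by logistic regression "using covariates for treatment, sex of the therapist, and experience of the practitioner", following the parallel psychodynamic trial. The same section adds random effects models and says that "Hypothesis 1 of this trial will be tested by the group*time interaction". In that test the T1 measurement is the reference against which T4 to T7 are coded. Among further analyses it lists "analyses of covariance of outcomes at T4 to T7 considering patient variables, taking into account potential differences between patients recruited by trained" and by untrained therapists, together with cross-sectional analyses across the three centres.

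**The concern.** Randomising therapists balances therapists in expectation. It does not by itself balance patients who reach a therapist afterwards by choice, referral or acceptance. The authors anticipate such patient differences but deal with them outside the model that tests the remission hypothesis.

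The covariates left out matter for this endpoint because remission is a fixed cut-off on the same scale that sets eligibility. Leaving out centre is a different and smaller matter. It concerns precision and correct standard errors under stratified randomisation, not selection.

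At stake is whether the estimated remission difference, tested one-sided at 0.05, reflects training alone or also a difference in case mix.

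**Working it through.** **1. Why entry severity and subtype matter (documents only).** Entry requires LSAS above 30, or above 60 for the generalised subtype; remission is 30 or below. The smallest fall that gives remission is 31 − 30 = 1 point at the lower threshold and 61 − 30 = 31 points at the generalised threshold. These are the two entry minima, not typical patients; the article gives neither the subtype mix nor the baseline distribution.

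**2. Does the baseline term in the group-by-time test help?** Every patient enters above 30, so remission at T1 is 0 for all. On the binary scale the baseline is a constant and carries no severity information. If the model is fitted to continuous LSAS, baseline LSAS is largely taken up, but subtype and centre are not.

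**3. How likely is a chance imbalance?** Inputs: 162 patients, 36 therapists, so 81 per arm and 4.5 per therapist. The SD of the difference in mean baseline severity, in SD units, is √(2 × DE / 81).
- Baseline ICC 0 (assumed): DE = 1, SD = 0.157, and P(|difference| ≥ 0.2) = about 20%.
- Baseline ICC 0.15 (assumed equal to the protocol's outcome ICC): DE = 1 + 3.5 × 0.15 = 1.525, SD = 0.194, and the probability is about 30%.

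**4. Size of the shift.** The protocol gives no figure to reproduce, so all inputs here are assumptions: remission 30%, imbalance 0.2 SD, no true treatment effect.

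*Probit form.* Shift = Φ(Φ⁻¹(0.30) + imbalance × baseline–outcome correlation) − 0.30.
- 0.2 SD, correlation 0.5: Φ(−0.524 + 0.10) − 0.30 = +3.6 points. In the opposite direction: Φ(−0.524 − 0.10) − 0.30 = −3.4 points.
- Range for a milder trained arm: +1.4 points (0.1 SD, correlation 0.4) to +6.5 points (0.3 SD, correlation 0.6).

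*Logistic form.* Therapist random effect at ICC 0.15; log-odds slope 0.5 to 1.0 per SD of severity.

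| Trained arm | Shift in remission difference |
|---|---|
| 0.2 SD milder | +1.8 to +3.4 points |
| no imbalance | 0 |
| 0.2 SD more severe | −1.8 to −3.2 points |

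Drop-outs count as non-remitters. If 30% is a completer rate, 25% drop-out dilutes the probit shift to 0.75 × 3.6 = 2.7 points.

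**5. Effect on the one-sided test, if the imbalance is systematic.** Normal approximation, effective n = 81 / 1.525 = 53.1 per arm, no true effect. A trained arm milder by 0.2 SD raises rejection from 5% to 7.5–10.2%. A trained arm more severe by 0.2 SD lowers it to 2.2–3.2%. A purely chance imbalance does not change the long-run 5%, because correct clustered standard errors already carry it; it does move the estimate in the trial actually run.

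**The case against.** The strongest reply is that nothing in the article shows an imbalance. Eligibility is confirmed before the patient chooses, patients do not know who was trained, and assessors are blinded. Masked choice among randomised therapists gives no systematic tilt. This stands. A reader might infer that self-selection builds a bias into the primary estimate, and the documents do not support that. What they leave open is chance with 36 clusters, and therapists who know their own allocation referring or accepting patients; the article itself speaks of patients recruited by one or other kind of therapist.

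Second, the section names a group-by-time test that includes baseline, and it plans a covariance analysis with patient variables. It would therefore be wrong to say that patient differences are ignored. But the first does not help on the remission scale (step 2), and the second leaves the remission model's own estimate unchanged.

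Third, the covariate set follows the parallel trial, whose comparability the authors value. That is a fair reason to keep the model as a sensitivity analysis. It is weaker as a reason to leave out prognostic patient variables and the stratification factor.

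Fourth, the precision gain must not be overstated. The usual reduction in residual variance from baseline adjustment applies to a continuous LSAS outcome. In a logistic model, adjustment changes the conditional odds ratio and does not shrink its standard error in that way.

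**Conclusion.** The point holds as a gap in the remission model, not as a demonstrated bias. As written, that model would carry through any arm difference in baseline severity or subtype. Under the assumed 30% remission and 0.2 SD imbalance, the remission difference moves by roughly 2 to 4 percentage points in whichever direction the imbalance lies; with no imbalance the shift is zero. Remission rate, imbalance and strength of association are all assumptions, since the article gives none of them. The rise in one-sided error applies only if the imbalance is systematic and favours the trained arm. Omitting centre affects precision and standard errors and is no source of selection bias. The change is worth making because its cost is low.

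**What to change.** In Primary analyses, add T1 LSAS (continuous), generalised versus non-generalised subtype, and centre (three levels) as fixed effects in the logistic model for remission. Keep the model with therapist covariates only as a sensitivity analysis, for comparability with the parallel trial.

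No new data are needed: LSAS and subtype are required for eligibility, and centre is the stratification factor. Eligibility is confirmed before a therapist is chosen, but T1 is described only as before treatment onset. The text should therefore say that the LSAS covariate is the value obtained before therapist choice, if that is the case.

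Costs:
- Four more parameters (1 + 1 + 2). At an assumed 30% remission, 162 patients give about 49 remitters. With treatment, sex and experience counted as one parameter each, the model goes from 3 to 7 parameters, or from about 16 to about 7 remitters per parameter.
- The odds ratio becomes conditional on these covariates, so the report should say so.
- LSAS and subtype overlap through the entry rule, so their separate coefficients should not be interpreted; the treatment estimate is what matters.

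A sensitivity analysis by referral source would address the therapist-referral route directly. The article does not say that referral source is recorded, and recruitment is under way, so this would be new data collection and is optional.

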#### Secondary analyses

Random effects analysis of treatment outcomes as a function of time will also be employed to analyze associations with questionnaire data and observer ratings (SPAI, SPK, SPV, BSPS, BDI, EQ-5D, ASQ, HAQ, STEPP, reaction to treatment, CGI). Moreover, analyses to be performed will include the following: cross-sectional analyses as above; analyses of subjects’ and therapists’ conditions regarded as subgroup; SP treatment costs (CSSRI)
[38] will also be considered as ‘process variables’; again, a one-sided level of significance at α = 0.05 will be chosen (see Discussion).

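### As worded, the repeated-measures test of Hypothesis 1 compares change from baseline; using the T1 score as a covariate is at least as precise in large samples and would cost only a change of wording

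*Protocol article*

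**What the plan says.** The protocol article's Primary analyses section contains two tests. The formal null hypothesis concerns remission probabilities, which are compared by logistic regression with treatment, therapist sex and practitioner experience as covariates. For repeated measures it plans random effects models and says: "Hypothesis 1 of this trial will be tested by the group*time interaction (with dummy variables coding the time effects at time points T4 to T7". The sentence ends by setting those dummies against the baseline measurement.

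The section neither names baseline LSAS as a covariate nor says that the arms share a common baseline mean. Among the further analyses it lists "analyses of covariance of outcomes at T4 to T7 considering patient variables", without saying which patient variables.

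Under Secondary analyses: "Random effects analysis of treatment outcomes as a function of time will also be employed" to examine a list of questionnaires and ratings. The group-by-time contrast against baseline is not repeated there.

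Under Randomization, therapists are randomised within centre. Patients are not randomised, but they "have no knowledge on whether or not the therapist they have freely chosen has been trained in manualized CBT". Under Participants, eligibility is confirmed before the patient picks a therapist.

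**The concern.** With T1 as the reference level of time and a free group effect, baseline is one of the responses and each arm has its own baseline mean. Each group-by-time coefficient then equals the difference between arms in mean change from T1. That fixes the weight on baseline at 1, whereas a covariate analysis estimates the weight from the data.

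Two things follow. The change estimate has a variance at least as large, so the test named for Hypothesis 1 may have less power and wider intervals than the collected data allow. And if the arms differ at baseline by chance, the change estimate moves with that difference, because part of it would have disappeared through regression to the mean anyway.

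**Working it through.** **The plan's own figure.** The Sample size calculation section uses N = 2 × [(z_alpha + z_beta)/ES]² × [1 + (m − 1) × ICC]. Its inputs are one-sided alpha 0.05, power 0.80, "we choose to expect a more conservative effect size of d = 0.50", five patients per therapist, and "the ICC was set to 15% which is high compared to similar studies". The effect is standardised by the "standard deviation of outcome". Putting these in: 2 × [(1.645 + 0.842)/0.5]² = 49.5; design effect 1 + 4 × 0.15 = 1.6; product 79.1, so 80 per group. The stated 58 is not reproduced. That is a separate matter. I use 58 below because it is the planned number, and show 80 as a check.

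**Variances at one follow-up time**, with the outcome SD set to 1, k = baseline SD/outcome SD, and rho = baseline-outcome correlation:

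- Covariate: V = 1 − rho².
- Change: V = 1 + k² − 2·rho·k = (1 − rho²) + (k − rho)².

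The excess (k − rho)² is never negative and is zero only at rho = k. Given a baseline difference D between arms, the expected shift of the change estimate is −(1 − rho/k) × D; at rho = 0.5 and k = 1 that is half of D.

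**Power** = Φ(0.5/SE − 1.645), with clustering handled in two ways:

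- (a) Design effect 1.6 on both analyses: SE² = 2 × 1.6 × V/58.
- (b) Therapist effect present only after baseline: SE² = 2 × [0.15 + (V − 0.15)/5]/11.6, with 58/5 = 11.6 therapists per group.

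The protocol gives neither rho nor k, so both are assumed over a range. Losses are in percentage points, from unrounded powers.

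| rho | k | V change | V covariate | (a) change / covariate | (a) loss | (b) change / covariate | (b) loss |
|---|---|---|---|---|---|---|---|
| 0.3 | 1.0 | 1.40 | 0.91 | 0.561 / 0.721 | 16.0 | 0.602 / 0.708 | 10.5 |
| 0.5 | 1.2 | 1.24 | 0.75 | 0.605 / 0.792 | 18.7 | 0.633 / 0.749 | 11.6 |
| 0.5 | 1.0 | 1.00 | 0.75 | 0.686 / 0.792 | 10.6 | 0.686 / 0.749 | 6.4 |
| 0.5 | 0.9 | 0.91 | 0.75 | 0.721 / 0.792 | 7.1 | 0.708 / 0.749 | 4.2 |
| 0.5 | 0.8 | 0.84 | 0.75 | 0.751 / 0.792 | 4.1 | 0.725 / 0.749 | 2.4 |
| 0.7 | 1.0 | 0.60 | 0.51 | 0.865 / 0.909 | 4.4 | 0.792 / 0.819 | 2.7 |
| 0.8 | 1.0 | 0.40 | 0.36 | 0.957 / 0.971 | 1.4 | 0.853 / 0.865 | 1.2 |
| 0.8 | 0.8 | 0.36 | 0.36 | 0.971 / 0.971 | 0.0 | 0.865 / 0.865 | 0.0 |

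At 80 per group, rho = 0.5 and k = 1, the losses are 8.9 (a) and 5.5 (b).

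**Checks.** In one simulated data set (58 per group, unclustered, T1 and T4 to T7 with common correlation 0.5), a random-intercept model with a free group effect gave interaction coefficients equal to the differences in mean change. The T4 standard error was 0.174, against 0.144 with T1 as covariate and 0.151 with the arms constrained to a common baseline mean. A cluster simulation (12 therapists of five patients per arm, rho = 0.5, k = 1, 4,000 runs) gave power of 70.7% against 81.0% under (a) and 71.2% against 77.1% under (b), losses of 10.3 and 5.9 points.

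**The case against.** **The size is not known.** A reader might infer a fixed loss of 6 to 11 points, or that change scores lose precision at every correlation below 1. Both need equal SDs at baseline and follow-up as well as an assumed rho. Entry requires LSAS above 30 (above 60 for the generalized subtype), which truncates baseline, while follow-up scores may fall freely, so k below 1 is plausible. At k = 0.8 and rho = 0.5 the loss is only 2 to 4 points. This objection stands, and the size must be given as a range. It does not reverse the direction, since the excess variance is a square.

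**The model is inferred.** The article does not say whether a group main effect is fitted, and a common-baseline model would recover most of the precision. This stands as a condition on the finding. A free group effect is the usual reading, and specifying the constraint would itself be one form of the fix.

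**It is not the powered test.** A reader might infer that the trial's main remission comparison is underpowered for this reason. The documents do not support that: the null hypothesis and the sample size concern remission, tested by logistic regression. The point is confined to the repeated-measures test, which the article nevertheless names for Hypothesis 1.

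**Patients choose their therapist.** If baseline differences were systematic, covariate adjustment would not automatically be the unbiased choice, and the article itself foresees possible patient differences between arms. But therapists are randomised, patients do not know who was trained, and eligibility is settled before the choice. Systematic imbalance is therefore not the leading expectation. What stands is that change from baseline is a choice of estimator, not an error.

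**Covariance analyses are already planned.** They are, but as further analyses and without naming baseline LSAS.

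**Secondary scales.** A reader might infer that every secondary scale is tested by the same contrast. The Secondary analyses section says only that outcomes are modelled over time. It does not show that measures such as alliance, session evaluation or reaction to treatment have a T1 value.

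**Conclusion.** The point holds in a limited form. On the usual reading, the test named for Hypothesis 1 is a difference in change from baseline. In large samples it is never more precise than a covariate analysis of the same data, and it moves with chance baseline imbalance unless rho = k.

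The size rests on two unstated quantities. With 58 per group, the loss runs from near zero (rho close to k) through 2 to 4 points (rho = 0.5, k = 0.8) and 6 to 11 points (rho = 0.5, k = 1) to about 10 to 16 points (rho = 0.3, k = 1). If baseline scores are the more variable, it can be larger: 12 to 19 points at rho = 0.5 and k = 1.2.

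This is an inexpensive gain in efficiency for the continuous LSAS analysis. It is not evidence that the test is invalid or that the remission comparison loses power.

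**What to change.** For continuous LSAS, and for those secondary scales that have a T1 value, model the post-baseline scores with T1 and its interaction with time as covariates, plus group, time, group-by-time and the planned random effects. Alternatively, keep T1 in the response and constrain the arms to a common baseline mean, which also retains patients with baseline data only.

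Report the group contrast at T4, the stated primary endpoint time, as the main contrast, with T5 to T7 alongside. Keep the change-from-baseline model as a sensitivity analysis; it also covers the worry about systematic differences from patient choice.

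The cost is a change of wording, with no new patients or data. Under the covariate version, patients with no post-baseline value leave the model; they carry almost no information on the treatment contrast.
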